### Project summary

The study will be conducted as a randomized feasibility trial with a follow up of 6 months. Participants will be employees diagnosed with cancer <2 years earlier, 18-63 years, currently in paid employment, and fully or partially sick-listed <1 year. Participants will be randomised to an intervention or a waiting list control group. The intervention itself targets the employer (i.e. supervisor, HR-manager or case-manager) of the included employee with cancer. The intervention can be seen as a ‘web-based intervention’. This web-based intervention, an online toolbox, is an open access website consisting of supportive information on how to guide employees with cancer throughout different return to work (RTW) phases. This supportive information consists of to-the-point text and video’s, and targets several actions of the employer, e.g. communicating effectively with the employee with cancer, assessing the employee’s work ability and supporting the employee with cancer emotionally. This study aims to assess feasibility of a future definitive randomised controlled trial (RCT) on the effectiveness of the MiLES intervention. Feasibility of a future definitive RCT was determined on the basis of predefined criteria related to method and protocol-related uncertainties (e.g. reach, retention, appropriateness). Also preliminary results on the effectiveness of the MiLES intervention will be obtained and the sample size needed in a future definitive RCT on the effectiveness of the MiLES intervention will be determined. The online toolbox will be considered effective if the intervention group improved significantly more on both components of the primary outcome measure ‘successful RTW’: the number of participants in the intervention group that return to work is higher compared with the control group, provided that their degrees of successfulness of RTW is also significantly higher. Data will be collected from 2019-01-01 to 2020-01-01. We expect a future definitive RCT to be feasible.

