### Rationale & background information

We have developed an employer-based intervention, named MiLES (an abbreviation of “the Missing Link: optimizing return to work of Employees diagnosed with cancer, by Supporting employers”) (1). By providing employers with support so as to improve their RTW guidance to cancer survivors, the MiLES intervention aims to enhance successful RTW of cancer survivors (1).

Tools that intervene at the intersection between employer and cancer survivor are scarce (2, 3), and studies to determine the effectiveness of such tools on survivors’ work outcomes are, to the best of our knowledge, absent in scientific literature (2, 3, 4). Several complicating aspects and uncertainties make it is essential to conduct a feasibility trial before conducting a future definitive trial on the effectiveness of the MiLES intervention on successful RTW of cancer survivors (5, 6).

The aim of this randomised feasibility trial is to assess feasibility of a future definitive RCT on the effectiveness of the MiLES intervention in terms of recruitment, reach, and acceptability of the study protocol. Secondary aims are: 1) to obtain preliminary results on the effectiveness of the MiLES intervention on successful RTW of cancer survivors, and 2) to determine the sample size needed in a future definitive RCT on the effectiveness of the MiLES intervention.

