### Study goals and objectives

The aim of this randomised feasibility trial will be to assess feasibility of a future definitive RCT on the effectiveness of the MiLES intervention in terms of recruitment, reach, and acceptability of the study protocol. Secondary, the study will also aim to evaluate the effectiveness of the online toolbox targeting employers on successful RTW of employees with cancer and to determine the sample size needed in a future definitive RCT on the effectiveness of the MiLES intervention. The online toolbox will be considered effective if the intervention group improved significantly more on both components of the primary outcome measure ‘successful RTW’: the number of participant in the intervention group that have returned to work is higher compared with the control group, provided that their degrees of successfulness of RTW is also significantly higher.

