### Methodology

Interventions: the intervention consists of an online toolbox targeting the participant’s employer. With ‘employer’ we refer to the person who is, from his/her role as (direct) supervisor, human resource manager or case-manager, in direct contact with the participant and from there responsible for guiding the participant at work. The online toolbox is an open-assess website containing to-the-point information, videos and checklists to support employers during the RTW process of an employee diagnosed with cancer.

Intervention group: participants randomised in the intervention group will be asked to inform their employer about the online toolbox, either by email or letter. Employers will be asked to use the online toolbox throughout the RTW process of the participant.

Control group: participants randomised to the control group will not inform their employer about the online toolbox for a period of six months.

Primary outcome measure: feasibility of a future definitive RCT on the effectiveness of the MiLES intervention (in terms of reach, appropriateness of inclusion criteria, recruitment rate and appropriateness of the study protocol).

Primary effect measure: the primary effect measure of the intervention is the combined effect measure successful RTW. This effect measure is a combination of RTW (having performed work activities in own work or in replacement work during the past four weeks) and a subgroup analyses for the ones that did return to work: degrees of successfulness of RTW (a new weighted, on individual level, outcome measure) (7). The degree of successfulness of RTW contains seven items, which were found to constitute successful RTW most importantly, according to employees diagnosed with cancer: ‘enjoyment in work’, ‘work without sacrificing health’, ‘open communication with employer’, ‘perceived confidence from employer without assumptions about workability’, ‘feeling welcome at work’, ‘good work-life balance’ and ‘joint satisfaction about the work situation (employer and employee)’. Each participant rates each items on its perceived importance and on its success. The combination of the items’ relative perceived importance and the items’ success determines the degrees of successfulness of RTW.

Secondary effect measures: Quality of Working life (QWLQ_CS) (8) and number of unwanted work changes (#).

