Time points data collection: baseline, before randomisation [T0], after 3 months of follow up [T1] and after six months of follow up [T2].

Randomization: using the electronic data-capture system Castor; allocation ratio will be set at 2:1 (intervention vs. control group); controlled the participant’s RTW status; neither the participant nor the research team will be blinded for the randomization.

Graphic outline: see figure 1.

[figure not shown]

**Figure 1.** Graphic outline of the study design and procedures using a flow diagram.

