### Data management and statistical analysis

Feasibility: a future definitive RCT to study the effectiveness of the MiLES intervention will be considered feasible when all of following criteria are met:

1. Criterion for appropriateness of inclusion criteria and for recruitment: ≥ 70% of the individuals who gave permission for telephone contact are willing to participate in the study;
2. Criterion for appropriateness of protocol: ≤ 20% do not want to participate due to the randomization procedure or are lost to follow-up due to randomization in the control group;
3. Criterion for appropriateness protocol: ≤ 20% of the participants are not willing to inform their employer about the online toolbox after randomization into the intervention group;
4. Criterion for retention rate: ≤ 20% of the participants are lost to follow-up; and,
5. Criterion for reach: the sample size number of 90 participants is included within the recruitment period of six months, starting when the first individual is invited by their treating physician.

Effect measures: equal distribution between the intervention and control group at baseline will be determined using chi-square tests for categorical variables and Student’s t-tests (normally distributed variables) or Mann-Whitney U tests (not normally distributed variables) for continuous variables. When no statistically significant unequal distributions will be found at baseline, the relative risk (RR) will be determined for RTW at T1 and T2, and a longitudinal multilevel analysis will be performed with the group classification as an independent variable and I-RTW_CS scores at the different time point (T0, T1 and T2) as dependent variables.

In the event of significant imbalance of a prognostic factor for the primary effect measure at baseline (9, 10), this factor will be used as a covariate for the analysis of that effect measure. In that case, a logistic regression analysis will be used to examine differences between the intervention and the control group with regard to RTW. For the subgroup of participants who did return to work, a longitudinal multilevel analysis will be performed to examine the difference between both groups with regard to I-RTW_CS scores. We hypothesised that participants in the intervention group 1) returned to work more often and 2) with a higher I-RTW_CS score, compared to the control group.

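### The effectiveness rule defines its return-to-work half as a higher number returning under 2:1 allocation, which is nearly always met with no effect; its two-test reading has no stated power basis.

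*Protocol*

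**What the plan says.** The Protocol states the effectiveness rule twice, in the Project summary and in Study goals and objectives. Each statement has three parts.

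- **Lead-in:** "The online toolbox will be considered effective if the intervention group improved significantly more on both components of the primary outcome measure".
- **RTW component:** "the number of participants in the intervention group that return to work is higher compared with the control group" in the Project summary, and "the number of participant in the intervention group that have returned to work is higher compared with the control group" in Study goals and objectives. Both clauses refer to a number, and neither asks for significance.
- **Score component:** "provided that their degrees of successfulness of RTW is also significantly higher".

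Other sections bear on the rule:

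- **Methodology, randomisation:** "allocation ratio will be set at 2:1 (intervention vs. control group".
- **Data management and statistical analysis:** RTW is compared by relative risk at T1 and T2, or by logistic regression if a prognostic factor is unbalanced at baseline. The I-RTW_CS score is analysed with a longitudinal multilevel model; the adjusted version is explicitly for those who returned to work. The sample size appears only as a reach criterion: "the sample size number of 90 participants is included within the recruitment period of six months".
- **Role of the effect results:** Rationale & background information lists among the secondary aims "to obtain preliminary results on the effectiveness of the MiLES intervention on successful RTW of cancer survivors", and Methodology gives "Primary outcome measure: feasibility of a future definitive RCT on the effectiveness of the MiLES intervention".

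**The concern.** The rule is inconsistent within one sentence. The lead-in asks for a significant improvement on both components, while the clause that spells out RTW asks only that a number be higher. When one arm is twice the size of the other, a higher number is expected with no effect at all, so that clause carries almost no evidence. It also differs from the analysis section, where relative risk and logistic regression both allow for arm size.

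The two readings fail in different ways:

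- **Literal reading:** the RTW half contributes nothing, and the word effective would rest on the score among returners alone.
- **Two-test reading:** a yes/no verdict is asked of about 90 people, with no power basis stated, in a trial that elsewhere calls these results preliminary. Failing the rule would then be the usual outcome for a modest true benefit.

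**Working it through.** **Inputs from the Protocol.** 90 participants at 2:1, so 60 intervention and 30 control. Up to 20% loss is tolerated (Data management and statistical analysis), giving 60 × 0.8 = 48 and 30 × 0.8 = 24.

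**Inputs assumed, because the Protocol gives none.** Two-sided 0.05 for each component; control RTW 50% to 70%; intervention 10 to 20 points higher; standardised I-RTW_CS difference d from 0.3 to 0.8 among returners. The figure of 90 has no accompanying power, alpha, rate or effect size, so it cannot be reproduced.

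**1. Literal reading: probability that the intervention count is higher.** With independent X ~ Bin(60, p_I) and Y ~ Bin(30, p_C):

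P(X > Y) = Σ_y P(Y = y) · P(X > y)

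| True RTW, intervention vs control | P(X > Y), 60 vs 30 |
|---|---|
| 20% vs 20% | 92.8% |
| 30% vs 30% | 97.6% |
| 40% vs 40% | 99.4% |
| 50% vs 50% | 99.9% |
| 60% vs 60% | 99.99% |
| 45% vs 60% (harm) | 96.6% |
| 40% vs 60% (harm) | 88.2% |
| 30% vs 50% (harm) | 70.9% |

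With 48 vs 24 and no effect, the probability is 89.9% at 20% and 99.7% at 50%. The expected counts are equal only when the intervention rate is half the control rate (60 × p_C/2 = 30 × p_C).

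**2. What the literal rule then tests.** With the count clause nearly always met, only the score test decides. By simulation (20,000 runs, 60 vs 30), the whole rule passes in about 2.4% of trials under the null (RTW 60% in both arms, d = 0), 42% for RTW 60% vs 75% with d = 0.5, and 81% for 60% vs 80% with d = 0.8.

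**3. Two-test reading, worked example (RTW 60% vs 75%, d = 0.5).**

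*RTW.* Pooled rate = (45 + 18)/90 = 0.70.

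- SE under the null = √(0.70 × 0.30 × (1/60 + 1/30)) = 0.1025.
- SE under the alternative = √(0.75 × 0.25/60 + 0.60 × 0.40/30) = 0.1055.
- Power = Φ((0.15 − 1.96 × 0.1025)/0.1055) = Φ(−0.48) = 31.5%.

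*Score.* Expected returners are 60 × 0.75 = 45 and 30 × 0.60 = 18.

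- Noncentrality = 0.5/√(1/45 + 1/18) = 1.79, on 61 degrees of freedom.
- Power = 42%.

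*Joint, taking the tests as independent.* 0.315 × 0.42 = 0.13 (simulation 12%). With 48 vs 24: 0.264 × 0.349 = 0.09.

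**4. Range of joint power over the assumed values, 60 vs 30.**

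| d | Joint power |
|---|---|
| 0.3 | about 2% to 14% |
| 0.5 | about 5% to 32% |
| 0.8 | about 11% to 57% |

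The lowest value is RTW 50% vs 60% with d = 0.3 (0.146 × 0.158 = 0.023). The highest is 70% vs 90% with d = 0.8 (0.655 × 0.866 = 0.567). With 48 vs 24 the overall range is about 2% to 44%.

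**5. Precision in the example.** RR = 0.75/0.60 = 1.25. SE of ln RR = √(0.25/45 + 0.40/18) = 0.167. The 95% CI is exp(ln 1.25 ± 1.96 × 0.167) = 0.90 to 1.73. For 80% power on RTW alone at 2:1, the same assumed rates need 336 participants before loss.

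**The case against.** The strongest defence is that no raw-count analysis is planned. The lead-in requires significance on both components, the closing clause can be read as implying that RTW must be significant too, and the analysis section compares RTW by methods that allow for arm size. On this view, number is loose wording for rate. That stands as an account of what was probably intended. It does not remove the defect: the analysis section gives no rule for turning a relative risk into a judgement of effective, and the two sections that do give one use a count.

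Three stronger readings are tempting, and the Protocol does not support them.

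- **That one half is met automatically and the whole rule is also rarely met.** These belong to alternative readings. If the count is taken literally, the rule is one score test with moderate to good power at d = 0.5 to 0.8. If both components must be significant, neither half comes free.
- **That an ineffective or harmful toolbox would readily be called effective.** Even literally, a significantly higher score is required, and the whole rule passes in only about 2.4% of trials under the null.
- **That a negative verdict would block the definitive trial.** The five feasibility criteria concern willingness to participate, acceptance of randomisation, willingness to inform the employer, retention and reach. None uses an effect result.

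It is also fair that a feasibility trial need not be powered for effects, and that a sample-size rationale may sit in a document not shown. The objection here is to attaching a significance verdict to results described as preliminary. Finally, the score calculation is a simple two-group comparison; the planned repeated-measures model could raise that power somewhat.

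**Conclusion.** The point holds as a defect in the wording and status of the effectiveness rule. The count clause is uninformative under 2:1 allocation: 92.8% to above 99.9% likely with no effect for RTW rates of 20% upwards at 60 vs 30, and 96.6% likely with a fall from 60% to 45%. These figures need only the arm sizes, the RTW rates shown and independent binomial counts.

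The two-test reading would usually return a negative answer for modest to moderate benefits, at about 13% joint power in the example. That figure rests on assumed rates, effect and alpha. The range of about 2% to 57% should be quoted with it, and its upper end needs very large effects on both components. A negative verdict would be uninformative in most of that range and sits badly with the preliminary status of the results.

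The rule serves a secondary aim. The primary feasibility outcome and its criteria are untouched.

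**What to change.** In both the Project summary and Study goals and objectives:

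1. Express the RTW component as the proportion returning, using the measures already planned: the relative risk at T1 and T2, or the adjusted odds ratio if logistic regression is used. Keep both time points.
2. Replace the effectiveness verdict with a statement that effects on RTW and I-RTW_CS will be reported as estimates with 95% confidence intervals and described as preliminary.
3. If the sponsor prefers to keep a rule, it should state explicitly that RTW must differ significantly in proportion. The low and assumption-dependent chance of meeting both conditions should then be acknowledged beside it.

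The cost is a change of wording in two sections, with no change to design, data collection or planned models. The sponsor gives up a yes/no effectiveness claim on a secondary aim.

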### Rationale & background information

We have developed an employer-based intervention, named MiLES (an abbreviation of “the Missing Link: optimizing return to work of Employees diagnosed with cancer, by Supporting employers”) (1). By providing employers with support so as to improve their RTW guidance to cancer survivors, the MiLES intervention aims to enhance successful RTW of cancer survivors (1).

Tools that intervene at the intersection between employer and cancer survivor are scarce (2, 3), and studies to determine the effectiveness of such tools on survivors’ work outcomes are, to the best of our knowledge, absent in scientific literature (2, 3, 4). Several complicating aspects and uncertainties make it is essential to conduct a feasibility trial before conducting a future definitive trial on the effectiveness of the MiLES intervention on successful RTW of cancer survivors (5, 6).

The aim of this randomised feasibility trial is to assess feasibility of a future definitive RCT on the effectiveness of the MiLES intervention in terms of recruitment, reach, and acceptability of the study protocol. Secondary aims are: 1) to obtain preliminary results on the effectiveness of the MiLES intervention on successful RTW of cancer survivors, and 2) to determine the sample size needed in a future definitive RCT on the effectiveness of the MiLES intervention.

### Study goals and objectives

The aim of this randomised feasibility trial will be to assess feasibility of a future definitive RCT on the effectiveness of the MiLES intervention in terms of recruitment, reach, and acceptability of the study protocol. Secondary, the study will also aim to evaluate the effectiveness of the online toolbox targeting employers on successful RTW of employees with cancer and to determine the sample size needed in a future definitive RCT on the effectiveness of the MiLES intervention. The online toolbox will be considered effective if the intervention group improved significantly more on both components of the primary outcome measure ‘successful RTW’: the number of participant in the intervention group that have returned to work is higher compared with the control group, provided that their degrees of successfulness of RTW is also significantly higher.

### Study design

Type of study: randomized feasibility trial

Inclusion criteria research population: diagnosed with cancer <2 years ago, able to fill out three questionnaires in the next six months, currently (partial) sick-listed for <1 year, of the working age (18-63 years), and in paid employment under a temporary (>6 months remaining) or permanent contract on part-time, full-time of flexible basis.

Exclusion criteria: not yet disclosed being diagnosed with cancer to the employer.

Expected duration study: one year (2019-01-01 until 2020-01-01).

### Methodology

Interventions: the intervention consists of an online toolbox targeting the participant’s employer. With ‘employer’ we refer to the person who is, from his/her role as (direct) supervisor, human resource manager or case-manager, in direct contact with the participant and from there responsible for guiding the participant at work. The online toolbox is an open-assess website containing to-the-point information, videos and checklists to support employers during the RTW process of an employee diagnosed with cancer.

Intervention group: participants randomised in the intervention group will be asked to inform their employer about the online toolbox, either by email or letter. Employers will be asked to use the online toolbox throughout the RTW process of the participant.

Control group: participants randomised to the control group will not inform their employer about the online toolbox for a period of six months.

Primary outcome measure: feasibility of a future definitive RCT on the effectiveness of the MiLES intervention (in terms of reach, appropriateness of inclusion criteria, recruitment rate and appropriateness of the study protocol).

Primary effect measure: the primary effect measure of the intervention is the combined effect measure successful RTW. This effect measure is a combination of RTW (having performed work activities in own work or in replacement work during the past four weeks) and a subgroup analyses for the ones that did return to work: degrees of successfulness of RTW (a new weighted, on individual level, outcome measure) (7). The degree of successfulness of RTW contains seven items, which were found to constitute successful RTW most importantly, according to employees diagnosed with cancer: ‘enjoyment in work’, ‘work without sacrificing health’, ‘open communication with employer’, ‘perceived confidence from employer without assumptions about workability’, ‘feeling welcome at work’, ‘good work-life balance’ and ‘joint satisfaction about the work situation (employer and employee)’. Each participant rates each items on its perceived importance and on its success. The combination of the items’ relative perceived importance and the items’ success determines the degrees of successfulness of RTW.

Secondary effect measures: Quality of Working life (QWLQ_CS) (8) and number of unwanted work changes (#).

Time points data collection: baseline, before randomisation [T0], after 3 months of follow up [T1] and after six months of follow up [T2].

Randomization: using the electronic data-capture system Castor; allocation ratio will be set at 2:1 (intervention vs. control group); controlled the participant’s RTW status; neither the participant nor the research team will be blinded for the randomization.

Graphic outline: see figure 1.

[figure not shown]

**Figure 1.** Graphic outline of the study design and procedures using a flow diagram.

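### Employees already working at T0 meet the RTW definition at entry, yet the default RTW analysis is a crude relative risk that ignores baseline RTW status

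*Protocol*

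**What the plan says.** All references are to the protocol.

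- **Definition.** Methodology defines the binary part of the primary effect measure as "RTW (having performed work activities in own work or in replacement work during the past four weeks". It sets no minimum hours and does not require a change from baseline.
- **Eligibility.** Study design admits employees "currently (partial) sick-listed for <1 year", and the Project summary has "fully or partially sick-listed <1 year". The one exclusion concerns disclosure of the diagnosis: "Exclusion criteria: not yet disclosed being diagnosed with cancer to the employer". Employees who are already working are not excluded.
- **Randomisation.** The Methodology section describes the allocation (2:1) as "controlled the participant’s RTW status".
- **Analysis.** Under Data management and statistical analysis, if no baseline imbalance is found, "the relative risk (RR) will be determined for RTW at T1 and T2". A covariate, through logistic regression, comes in only conditionally: "In the event of significant imbalance of a prognostic factor for the primary effect measure at baseline". The multilevel model for the success score uses "I-RTW_CS scores at the different time point (T0, T1 and T2) as dependent variables", so that score is expected to exist at baseline for at least some participants.
- **Use of the result.** Study goals and objectives asks for a significantly greater improvement on both components of successful RTW, and also makes the sample size of a definitive trial an aim.

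**The concern.** A partially sick-listed employee who has done any work in the four weeks before T0 counts as returned to work at entry. On the binary component this participant cannot improve. The protocol evidently expects such participants: controlling randomisation for RTW status makes sense only if that status varies beforehand, and a success score meant for people who have returned is analysed at T0.

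The default RTW analysis makes no use of this. It mixes two questions in one ratio: whether people off work start working, and whether people at work keep working. Balancing the arms on RTW status prevents confounding but does not separate the two questions. It also makes a significant imbalance in RTW status unlikely, and that imbalance is the only route by which the variable would enter the model.

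At stake are the reading of the RTW half of the effectiveness rule and the usefulness of the observed rates for planning the definitive trial.

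**Working it through.** **Plan's own figure.** The protocol gives 90 participants as a recruitment target, without RTW rates, effect size, alpha or power. There is nothing to reproduce.

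**Inputs from the protocol.** 90 participants at 2:1, so 60 intervention and 30 control; RTW assessed at T1 and T2.

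**Assumed inputs (none is in the protocol).**
- Share working at T0: f = 30%, 50% or 60%, equal in both arms.
- Those working at T0: 95% still working later, in both arms.
- Those not working at T0: 60% (intervention) versus 40% (control) return, so RR = 0.60/0.40 = 1.50.
- Two-sided alpha 0.05; complete outcome data.

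**Step 1: rate seen in each arm.** Overall rate = f × 0.95 + (1 − f) × p.

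| f | Intervention | Control | Crude RR |
|---|---|---|---|
| 30% | 0.285 + 0.70 × 0.60 = 0.705 | 0.285 + 0.70 × 0.40 = 0.565 | 1.25 |
| 50% | 0.475 + 0.50 × 0.60 = 0.775 | 0.475 + 0.50 × 0.40 = 0.675 | 1.15 |
| 60% | 0.570 + 0.40 × 0.60 = 0.810 | 0.570 + 0.40 × 0.40 = 0.730 | 1.11 |

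The risk difference shrinks from 20 points to (1 − f) × 20 = 14, 10 and 8 points.

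**Step 2: other assumed rates.** With 70% versus 50% among those not working (RR 1.40) and everyone at work staying there, f = 20%, 40% and 60% give 0.76/0.60 = 1.27, 0.82/0.70 = 1.17 and 0.88/0.80 = 1.10. The direction is the same.

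**Step 3: power at f = 50%, by simulation.**
- Crude test on 60 versus 30: 14%.
- Restricted to those not working at T0, 30 versus 15: 23%.
- Mantel-Haenszel test stratified by T0 RTW status, all 90 kept: 21%.

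**Step 4: what stratifying does and does not recover.** With the same 2:1 split in both strata, the Mantel-Haenszel pooled RR is (0.95 + 0.60)/(0.95 + 0.40) = 1.15, the same as the crude RR. Stratifying sharpens the test, but only the stratum-specific results show the 1.50.

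**Step 5: definitive trial at f = 50%** (80% power, 1:1, n per arm = [1.96√(2p̄(1 − p̄)) + 0.84√(p₁(1 − p₁) + p₂(1 − p₂))]² / (p₁ − p₂)²).
- Crude mixed rates, 77.5% versus 67.5%: 312 per arm.
- 60% versus 40% among those not working: 97 per arm. Under the present eligibility this means enrolling about 97/0.50 = 194 per arm.

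**Step 6: precision in the not-working stratum.** With 18/30 versus 6/15, SE(log RR) = √(0.4/18 + 0.6/6) = 0.350. The 95% CI is 1.50 × exp(±1.96 × 0.350) = 0.76 to 2.98.

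**The case against.** **The dilution depends on a null effect in those at work.** The Project summary says the toolbox addresses several RTW phases, so helping partial returners stay at work is a plausible target. If 95% versus 85% stayed (f = 50%), the overall rates would be 77.5% versus 62.5%, RR 1.24, needing about 146 per arm, fewer than the 194 enrolled. This stands: the pull toward 1 is conditional.

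**The mixed rates are not wrong for planning.** A reader might infer that they would mislead the definitive trial's sample size. The protocol does not support this: a definitive trial with the same eligibility, endpoint and crude analysis would see those same rates, and 312 per arm would be the right answer under the assumptions. They mislead only if the population or analysis changes. Nor is 312 against 97 like for like; in enrolled participants it is 312 against about 194.

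**The affected share is unknown.** A reader might also infer that every partially sick-listed participant already meets the definition, or that they form a large part of the sample. The protocol says neither. Some may have done no work in the preceding four weeks, and no T0 share is given.

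**Part is already handled.** Allocation guards against confounding by RTW status, and participants at work can still improve on the success score. This stands, but it leaves the crude RR mixing two questions.

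**Restricting the analysis to those not working** is not clearly better. It gains little power over the stratified test (23% versus 21%), drops half the sample at f = 50%, and leaves those at work out of the RTW component of the effectiveness rule.

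**Conclusion.** The point holds in a limited form. The protocol's definition, eligibility rule and default crude RR together mean that participants working at T0 cannot improve on the RTW component. Baseline RTW status is used in the allocation but not, by default, in the analysis. This is an interaction between choices that the protocol itself fixes, not a detail left for a statistical analysis plan.

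If the toolbox does little for staying at work, an RR of 1.50 among those not working appears as 1.25 to 1.11. That range rests on an assumed T0 share of 30% to 60%, 95% staying at work in both arms, and 60% versus 40% among the rest.

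It should be fixed, but it does not threaten the trial. Effectiveness is a secondary aim of a feasibility study, low power at 90 is not itself a defect, and none of the five feasibility criteria uses the RTW rate.

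**What to change.** In Data management and statistical analysis:

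1. Analyse RTW at T1 and T2 stratified by, or adjusted for, T0 RTW status, regardless of whether a baseline imbalance is found.
2. Report separately the RR for new return to work among those not working at T0, and staying at work among those working at T0. A pooled stratified RR alone would not show the difference between the two.
3. For the definitive sample size, give event rates by arm within each stratum together with the share working at T0, so that planners can compare populations and analyses in terms of participants enrolled.

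**Cost.** Wording only; RTW status is already needed for randomisation. The downside is that stratum-specific estimates will be imprecise (95% CI about 0.76 to 2.98 in the example with 30 versus 15), and more so with the loss to follow-up of up to 20% that the criteria tolerate. They should be presented as descriptive.
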